### Image analysis

#### Reporting of conventional imaging

The conventional imaging (^18^F-choline PET-CT, CT-CAP and ^99m^Tc Bone Scan) will be independently reported by two radiologists and nuclear medicine physicians, later reviewed in consensus to clarify any discrepant findings. The report will be transferred to a proforma and final nodal (N) and metastatic (M) stages will be derived base on the reported proforma.

#### Comparison of conventional imaging with WB-MRI

The research team will correlate the conventional imaging proforma with the baseline WB-MRI proforma and follow-up WB-MRI findings. The radiologists and nuclear medicine physicians in consensus will review all discrepancies, between conventional and WB-MRI scans. Anatomical matching errors resulting from discrepancies in ascribing disease location will be recorded and corrected [33]. Residual discrepancies will be highlighted, categorised as perceptual and technical and statistically assessed [33]. The per-patient sensitivity and specificity of WB-MRI will be determined against the enhanced reference standard before and after correction for any anatomical matching discrepancies and perceptual errors.

Patients who are unable to attend the 1 year follow up WB-MRI may not be included in the diagnostic accuracy analysis. Efforts will be made to minimise amount of missing data. A statistician’s advice will be sought especially on how to manage ‘missing not at random’ data (if any).

### Sub-study analysis

#### The significance of the human epidermal growth factor receptor (HER) activated dimer

The blood sample will be used to investigate the significance of the Human Epidermal growth factor Receptor (HER) activated dimer in recurrent prostate cancer. Up-regulation of the HER1 (EGFR)/HER3 dimer was recently found, for the first time, to limit the efficacy of anti- epidermal growth factor receptor (EGFR) treatment in human breast cancer, as directly shown by imaging of residual disease; suggesting the potential of combined EGFR/HER3-targeted treatment [34]. This molecular signalling rewiring is hypothesised to constitute a pathway of resistance to hormonal treatment in prostate cancer as well. We intend to quantify the EGFR/HER3 heterodimer using fluorescence lifetime imaging microscopy (FLIM) in formalin-fixed prostate cancer tissues as well as in matched circulating exosomes from patient-derived plasma. We will then correlate the heterodimer quantification with tumour genomic changes such as phosphatase and tensin homolog (PTEN) mutation/deletion. The patient-derived correlative experiments will be complemented by mechanistic in vitro experiments that investigate the effect of EGFR and phosphatidylinositol 3-kinase (PI3K)/AKT inhibitors on HER dimer formation in castration-resistant and sensitive prostate cancer cells, and their exosomes released into the culture supernatants. In the clinical setting, the tissue and exosome-derived HER dimer measurements will be combined with WB-MRI findings to assess their value and translation as predictive biomarkers of clinical outcome and response to treatment.

#### Heterogeneity (across metastatic sites) of WB-MRI signals for prediction of ADT response

For patients undergoing ADT treatment, retrospective quantitative analysis of WB-MRI’s ADC and FF signal intensities will be performed to derive heterogeneity indices across confirmed true positive metastatic sites. The heterogeneity indices will inform Bayesian models to predict high-risk patients with aggressive disease that progress on ADT within 12-months of treatment.

### Health economic analysis

The health economic analysis will compare the incremental costs and effects of WB-MRI for metastatic disease detection compared with conventional imaging from a national health service (NHS) perspective and thus determine whether it is an efficient use of NHS resources. From an economic viewpoint, the cost-effectiveness of WB-MRI versus conventional imaging is determined by two main stages of the pathway: the treatment decision pathway and the treatment pathway (and its associated disease pathway). The former includes the time from presentation to treatment decision by the clinician and includes the imaging tests received; the latter includes the time period following the treatment decision and subsequent disease progression. In patients for whom the treatment decision with WB-MRI is the same as that with conventional staging, the subsequent disease pathways will be the same. Where the treatment decision with WB-MRI is different, the disease pathway will be different, yielding potentially different costs and health outcomes (and hence the patient’s quality of life).

The precise nature of the economic analysis will therefore depend on the degree of concordance between treatment decisions provoked by WB-MRI versus conventional imaging.

#### Scenario 1

There is concordance between the treatment decisions associated with WB-MRI and conventional imaging. In this case, the cost components included in the analysis will be conventional metastases imaging tests (as described above) and the costs of treating adverse events associated with conventional staging. The volume of resource use and unit costs will be taken from standard published sources, hospital administrative datasets and from trial data. Since the two algorithms yield the same treatment decisions, cost-effectiveness depends on the incremental cost only of WB-MRI versus conventional imaging.

#### Scenario 2

There is discordance between the treatment decisions associated with WB-MRI and standard imaging. In this case, cost-effectiveness depends on the incremental cost and effects of the treatment decision pathway and the subsequent disease pathway associated with WB-MRI versus conventional staging.

The economic evaluation will also take into consideration the accuracy of WB-MRI versus conventional standard imaging techniques. Specifically, we will model the consequences, in both costs and effects, of true positives, false positives, true negatives and false negative outcomes. Thus, the economic study will evaluate both clinical and economic consequences of the novel imaging technique.

Cost-effectiveness will be calculated as the mean cost difference between WB-MRI versus conventional imaging divided by the mean difference in outcomes (as measured quality-adjusted life years; QALYs) to give the incremental cost-effectiveness ratio (ICER). Also, a cost-consequence analysis will be performed by calculating the mean incremental costs per incremental gain (or loss) in clinical natural units, for example cost per metastases identified.

Finally, to address uncertainty in our clinical and economic parameters, we will perform a comprehensive set of sensitivity analyses on our model estimates. Probabilistic sensitivity analysis using non-parametric bootstrapping methods will be performed. Outputs from this will inform a cost-effectiveness acceptability curve, which shows the probability that WB-MRI is cost-effective at different values of the NHS’ willingness to pay for an additional QALY. We will also subject the economic model to extensive one-way sensitivity analysis to identify key parameters that drive cost-effectiveness.

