**Fig. 1 Fig1:**
[figure not shown]
Trial flowchart. The trial flowchart describing the standard of care pathway through which patients were reviewed and clinical decisions made. A parallel research pathway was designed to mimic the standard pathway without interfering in patient care except when clinically significant incidental findings are identified

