### Trial interventions

#### Whole body MRI

Recruited patients will have WB-MRI scan on presentation with BCR and then at 12 months (follow-up). All WB-MRI scans will be performed at University College London Hospital NHS foundation trust (UCLH) imaging department on a 3.0 T scanner (Ingenia; Phillips Healthcare, Best, Netherlands), using a fixed protocol (Table 1). For participants’ comfort, the WB-MRI protocol will be limited to a maximum of 1-h scan time.

**Table 1 Tab1:** Whole Body MRI sequence parameters

	T2-TSE	mDixon (pre- and post-contrast)	DWI (b0, 1000)
Slice orientation	Transverse	Coronal	Transverse
Echo time (ms)	80	2.303	17
Repetition time (ms)	1214.69	3.5	6304.5
Space between slices	5.5	2.5	5.5
Number of slices	40	120	40
Slice thickness (mm)	5	5	5
Acquisition matrix	500*497	240*238	124*118
Echo train length	89	2	39
Number of averages	1	1	2
Pixel bandwidth (Hz)	538	1847	3354
Pixel spacing	0.78/0.78	1.04/1.04	2.08
Flip angle	90	15	90

*TSE* Turbo spin echo, *DWI* Diffusion weighted imaging

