### Health economic data collection

Data collection for the health economic analysis will be primarily concerned with cost data associated with the diagnosis and treatment of metastatic prostate cancer. Routinely collected administrative data from UCLH will be used to determine the relevant costs associated with the diagnostics test. To determine the consequence of detected metastatic disease on the treatment pathway, clinical experts will be interviewed, and patient notes will be reviewed noting changes to medication, radiotherapy, surgery, outpatient visits, inpatient visits and day cases, where possible. Data from existing trials such as STAMPEDE [24] and FORECAST [7] will be used to inform other economic parameters such as the health-related quality of life as these are not being collected in LOCATE.

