### Reporting of trial imaging

#### Initial WB-MRI scan

The study will be reported by two experienced radiologists, blinded to all other imaging investigations, initially independently and then in consensus using a locked sequential read paradigm (LSR). The images will be reviewed for the presence of nodal (N) and metastatic (M) disease and each radiologist will record the presence/absence of disease on the study-specific proforma.

The initial WB-MRI read results will not be revealed to the clinical team. Where a significant additional/incidental finding is demonstrated this will be reported as per standard clinical practice and relayed to the clinical team.

A 1–6 Likert scale [23, 25] will be used for scoring as has been previously described for WB-MRI studies. 1 – disease definitely not present, 2 – probably not present, 3 – possibly not present, 4 – disease possibly present, 5 – probably present and 6 – definitely present.

Scoring will be conducted based on evaluation of imaging features of lymph nodes and bone metastases as indicated below in Table 2 .

**Table 2 Tab2:** Features suggestive of adverse and benign changes in both nodes and bones

	Benign features	Adverse features
Node	Lymph node <5 mm in short axis diameter (SAD) with no concerning features on DWI, T2 weighted or contrast enhanced imaging and definite benign features e.g. (i) Fatty hilum, (ii) Oval nodal morphology with clearly defined and (iii) Regular nodal border and contours.	Concerning features could be described as (i) Size above normal limit e.g. > 10 mm for most, (ii) Loss of fatty hilum, (iii) Irregular border, (iv) Asymmetric high DWI signal intensity, (v) Low T2 signal
Bone	Normal appearing bone with uniform moderate-high signal on T1 weighted imaging and low-moderate signal on T2 weighted imaging. Focal lesions demonstrating clearly incidental/benign multiparametric signal characteristics and/or location	(i) Increase in DWI high b-value signal vs. background noise. (ii) Low signal intensity on T1 and (iii) Intermediate to high signal intensity on T2 (iv) Lesional contrast enhancement

*DWI* Diffusion weighted imaging

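### The Scenario 1 cost list names only conventional imaging and its adverse events, so it cannot give the incremental cost of WB-MRI that the same paragraph relies on

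*Protocol article*

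**What the plan says.** All references are to the protocol article.

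- **Health economic analysis, Scenario 1** applies when the two pathways give the same treatment decision. It states that "the cost components included in the analysis will be conventional metastases imaging tests (as described above") together with "the costs of treating adverse events associated with conventional staging". The paragraph ends by saying that "cost-effectiveness depends on the incremental cost only of WB-MRI versus conventional imaging".
- **Whole body MRI, Table 1** includes a sequence headed "mDixon (pre- and post-contrast"), so WB-MRI is a contrast-enhanced examination.
- **Initial WB-MRI scan** keeps the staging result from the treating team ("The initial WB-MRI read results will not be revealed to the clinical team") but makes an exception: "Where a significant additional/incidental finding is demonstrated this will be reported as per standard clinical practice and relayed to the clinical team".
- **The legend of Fig. 1** repeats the exception. The research pathway runs "without interfering in patient care except when clinically significant incidental findings are identified".
- **Health economic data collection** takes test costs from routine hospital data. To trace what follows from finding metastatic disease, it adds expert interviews and a review in which "patient notes will be reviewed noting changes to medication, radiotherapy, surgery, outpatient visits, inpatient visits and day cases".

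**The concern.** The Scenario 1 sentence states which costs enter, and every item belongs to the conventional pathway. Adverse-event costs are judged relevant enough to name, but for one strategy only. The plan itself describes two further sources of WB-MRI cost: a contrast-enhanced scan, and incidental findings that can change a man's care.

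This matters most in Scenario 1. Because decisions agree, there is no difference in effects, and the conclusion rests on a cost difference alone. Any cost left out on one side moves that difference by its full amount. The Discussion says the trial should guide possible NHS use of WB-MRI and define the most cost-effective pathway, so the incremental cost will be read as a decision figure.

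**Working it through.** The plan states no figure for this comparison, so there is nothing to reproduce. The check compares the cost list with the quantity it is meant to deliver.

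**Notation** (expected cost per man; w = WB-MRI, c = conventional imaging): T = the tests, A = treating adverse events of the tests, I = working up incidental findings from the tests.

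**Step 1. Full incremental cost when decisions agree.**
D(full) = (Tw + Aw + Iw) − (Tc + Ac + Ic).

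**Step 2. The list taken literally.** Only Tc and Ac are named, so D(literal) = 0 − (Tc + Ac). This has no WB-MRI term and is not an incremental cost of WB-MRI. The list contradicts the paragraph's own conclusion.

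**Step 3. The list with the WB-MRI test restored**, since routine hospital data are to supply test costs.
D(restored) = Tw − (Tc + Ac).

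**Step 4. Remaining error.**
D(restored) − D(full) = −Aw − (Iw − Ic).

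- The first term, −Aw, is zero or negative. Leaving out WB-MRI adverse events while counting conventional ones makes WB-MRI look cheaper.
- The second term can have either sign. The list names incidental work-up for neither strategy. Contrast CT of chest, abdomen and pelvis and PET-CT (sections Computed tomography and PET-CT) may also show incidental findings. If Iw exceeds Ic, the omission favours WB-MRI; if Ic exceeds Iw, it counts against WB-MRI.

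**Step 5. Size.** An omitted item costs p × k per man, where p is the share of men affected and k the cost per case. The document gives neither. Purely as an assumption, take p from 2% to 30% and k from 100 to 1,000 currency units:

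- lowest: 0.02 × 100 = 2 per man;
- highest: 0.30 × 1,000 = 300 per man.

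This 150-fold range (300 / 2) shows only that the size cannot be fixed from the document. For incidental work-up it is also a gross WB-MRI cost, before subtracting the conventional counterpart Ic.

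**Step 6. Is the gap filled elsewhere?** The later part of Health economic analysis models costs and effects of true and false positives and negatives. Under Derivation of enhanced reference standard, these categories refer to metastatic disease status. They cover misclassified metastases, but not scan or contrast events, nor incidental findings unrelated to staging. Scenario 2 gives no component list, so it shows no asymmetry, but it does not supply the missing items either.

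**The case against.** The strongest reply is that the sentence is loosely drafted and was never meant to be exhaustive. It leaves out even the WB-MRI scan, without which no comparison is possible, and Health economic data collection provides for test costs. A condensed article may also leave the full list to an economic plan that is not shown. This has force: the missing scan cost is probably a slip, and the absence of extraction details such as a trigger field is not in itself a defect. It does not dispose of the point. The sentence says what the components will be, names adverse events for one side only, and no other section shown restores the WB-MRI side.

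Three stronger readings are tempting but not supported:

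- **That work-up triggered by WB-MRI will be charged to conventional imaging.** Every man follows the standard pathway, so a reader might infer that these costs end up in the comparator and that the error doubles. The notes review, however, is directed at the consequences of detected metastatic disease, and no section says incidental work-up is booked to conventional imaging. Scenario 1 also draws on hospital datasets and trial data, so the risk is conceivable, but it remains an inference.
- **That every omission favours WB-MRI.** This holds for the one-sided adverse-event count. It does not hold for incidental work-up, where only the difference between pathways matters.
- **That the harms of WB-MRI are ignored altogether.** The consequences of false-positive and false-negative results are modelled.

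**Conclusion.** The point holds in a limited form. The Scenario 1 list is one-sided and inconsistent with the incremental cost it is meant to support. As written it omits the WB-MRI test, WB-MRI scan and contrast adverse events, and work-up of relayed incidental findings. The adverse-event asymmetry biases the incremental cost towards WB-MRI by Aw per man. The incidental-finding omission shifts it by Iw − Ic, with unknown sign. Neither can be sized from the document, and the bias could be small.

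This conclusion assumes that the list is applied as stated, apart from the evident need for a WB-MRI test cost. Only the secondary cost-effectiveness objective is affected; sensitivity and specificity are not. The correction is worth making because the defect lies in a stated rule, bears directly on a cost-only comparison, and is cheap to remove. According to Study status, data were still being collected and the full analysis had not begun.

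**What to change.** Replace the Scenario 1 list with one that applies equally to both strategies, and use it also for the decision-pathway part of Scenario 2:

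- the imaging tests of each strategy;
- treatment of adverse events of each test, including contrast events;
- work-up of incidental findings from each test.

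Add an attribution rule: work-up triggered by a WB-MRI finding relayed to the clinical team is costed to the WB-MRI strategy, and work-up triggered by a conventional test to the conventional strategy. A finding shown by both is costed to both, since either test alone would have led to the work-up. One trigger field in the resource-use extraction is enough to apply the rule. Rates and unit costs for the adverse-event and incidental items can go into the one-way sensitivity analyses already planned.

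The cost is a wording change and a little more extraction work. The incremental cost may become less favourable to WB-MRI. No scan, visit or clinical procedure changes.

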## Discussion

At the time of writing, the LOCATE trial is the largest prospective multi-centre trial to compare WB-MRI with conventional imaging pathway specifically in patients with radio-recurrent prostate cancer.

The LOCATE trial will be informative because it compares comprehensive imaging pathways and takes into consideration the cost-effectiveness of each pathway. This trial will therefore provide valuable information to guide potential implementation of new imaging platforms for prostate cancer management pathways.

The results from the LOCATE trial would be relevant to the current clinical management pathway, specifically, should WB-MRI be advocated in the NHS in the setting of BCR.

The LOCATE trial design includes important features: unlike most other trials, the initial finding on WB-MRI will be validated using 1 year follow up WB-MRI scans, corroborating the findings on initial scan in the context of patient management. In this way, we minimise the potential overcalling of disease positivity by WB-MRI that could lead to an overestimated sensitivity of WB-MRI compared to conventional imaging techniques.

Additionally, and in order to define the most cost-effective imaging pathway for the health care system, we will perform an economic evaluation which includes a comprehensive set of sensitivity analyses to identify uncertainty in both clinical and economic estimates. Whilst recent trial designs incorporating WB-MRI are including health economic analysis [35–38], such information is still unavailable for prostate cancer imaging pathways.

The LOCATE study has some potential limitations. Firstly, we are using a combined biochemical/imaging follow-up to derive an enhanced reference standard against which the results of WB-MRI will be analysed. Although histopathological confirmation would have been preferable in cases where a discrepancy exists between WB-MRI and conventional imaging tests, such approach is technically challenging and ethically not feasible [39].

Secondly, whilst the qualitative and metastatic staging findings can be generalised to other imaging platforms, such generalisability would be limited in quantitative biomarker imaging analyses (heterogeneity index). However, ongoing work is being carried out to improve standardisation of quantitative MRI imaging across different platforms that could ultimately aid in generalisation of such technique [39, 40].

Finally, it is important to note that ^68^Ga-PSMA PET-CT within a short time has led to significant advances in prostate cancer imaging both in primary and recurrent settings [41, 42]. However, there is yet to be large prospective multi-centre studies to assess its diagnostic accuracy in comparison to WB-MRI, and the start of the LOCATE trial predated availability of ^68^Ga PSMA PET-CT at our institution and therefore a head to head comparison was not possible. More importantly, there is significant cost difference between the two modalities and PSMA is routinely not available in many centres in the UK.

### Study status

At the time of submission, the study is currently at the data collection stage and full trial data analysis is expected to begin shortly.

## Data Availability

Not applicable.

## Abbreviations

ACD: Acid citrate dextrose
ADC: Apparent diffusion coefficient
ADT: Androgen deprivation therapy
BCR: Biochemical relapse
BRT: Brachytherapy
CT: Computed tomography
DWI: Diffusion weighted imaging,
EBRT: External beam radiotherapy
EDTA: Ethylenediaminetetraacetic acid
EFGR: Epidermal growth factor receptor
EPI: Echo planar imaging
FACS: Fluorescence-activated cell sorting
FF: Fat fraction
FLIM: Fluorescence lifetime imaging microscopy
HER: Human epidermal growth factor receptor
ICER: Incremental cost-effectiveness ratio
MDT: Multi-disciplinary team
MRI: Magnetic resonance imaging
NHS: National health service
PACS: picture and archiving system
PBMC: Peripheral blood mononuclear cell
PCa: Prostate cancer
PET: Positron emission tomography
PI3K/AKT: Phosphatidylinositol 3-kinase
PSA: Prostate specific antigen
QALY: Quality-adjusted life year
TSE: Turbo spin echo
WB-MRI: Whole-body magnetic resonance imaging
